**Fig 1 pone.0324089.g001:**
[figure not shown]
Procedure, measures and study design. **A.** Procedure and measures. Questionnaires include the informed consent form (ICF), a demographic survey and stress and pain related constructs (i.e., questionnaires). Biochemical measures include five saliva samples during the lab assessment to measure cortisol, oxytocin and alfa-amylase and include one hair cortisol sample. Experimental pain measures include CPM (conditioned pain modulation), TSP (temporal summation of pain), HPSTh (heat pain suprathreshold) and PPTh (pressure pain threshold). Physiological stress measures include HR(V) (heart rate (variability)), BP (blood pressure), RR (respiratory rate), SC (skin conductance) and ST (skin temperature). Neural measures include structural MRI, RS-fMRI (resting-state fMRI), task-based fMRI (experimental pain – functional MRI), DWI (diffusion-weighted MRI) and pCASL (Pseudo-Continuous Arterial Spin Labeling). Before and after stress induction, using the TSST (Trier Social Stress Test), VAS (Visual Analogue Scale) and PANAS (Positive And Negative Affect Schedule) are acquired. **B.** Study design. After enrollment and the lab assessment (as displayed in A), participants collect five saliva samples at home throughout the day for three consecutive days. The chronic and subacute low back pain groups are tested again, using the same test-battery, after a follow-up period of six months.

### 2.4. Assessments of stress

Both non-induced (basal) and experimentally induced stress responses, and both acute (via self-reports, ANS measures and salivary hormonal levels) and chronic (via hair cortisol) states will be measured.

#### 2.4.1 Self-reported stress.

An overview of the stress-related trait questionnaires and timing of administration can be found in Table 1.

**Table 1 pone.0324089.t001:** Overview of the validated stress- and pain-related questionnaires.

Questionnaire	Domain	Timeline		
		Screening	Baseline	6-month follow-up
**Hospital Anxiety and Depression Scale** [33]	Anxiety and depression			
**Pain Anxiety Symptoms Scale-20** [34]	Fear and anxiety specific to pain			
**Pain Catastrophizing Scale** [35]	Pain catastrophizing			
**Pain Disability Index** [36]	Daily functioning related to pain			
**Pain Vigilance and Awareness Questionnaire** [37]	Attention to pain			
**Brief Resilience Scale** [38]	Recovery or bouncing back from stress			
**Intolerance Uncertainty Scale-12** [39]	Responses to uncertainty, ambiguous situations and the future			
**Perceived Stress Scale** [40]	Perception of stress			
**Stress Mindset Measure** [41]	Perception of stress as enhancing or debilitating			
(Shortened) **Pittsburgh Sleep Quality Index** [42]	Sleep quality			
**Childhood Trauma Questionnaire** [43]	Childhood trauma			

A VAS will be used to assess the effects of the acute stress induction on self-perceived stress (see Fig 1). The VAS will range from zero to 100 mm, with zero representing “no stress at all”, and 100 representing “most stress imaginable” [44]. The change in self-perceived stress will be calculated by subtracting VAS-scores (Δ self-perceived stress = post-stressor VAS-scores – pre-stressor VAS-scores).

Positive and negative affect will be assessed using the Positive and Negative Affect Schedule (PANAS) [45]. The change in positive and negative affect due to a stressor will be calculated by subtracting PANAS values (Δ positive and negative affect = post-stressor values – pre-stressor values) [4]. The PANAS consists of ten questions concerning positive affect, and ten questions concerning negative affect. Each question is scored between one and five, with one being “very slightly or not at all”, and five being “extremely”. For both categories, the final score ranges between ten and 50, with higher scores representing higher levels of positive or negative affect.

Participants will fill out the Primary Appraisal Secondary Appraisal (PASA) to examine their perception of an upcoming stressor, either as threatening or challenging, using a Likert scale [46].

#### 2.4.2 ANS measures – acute autonomous stress markers.

Saliva will be collected using a synthetic Salivette (Sarstedt, the Netherlands) at several time points across the lab assessment (see also 4.4). Participants will be instructed to place the synthetic swab in their mouths under the tongue for two minutes until it becomes saturated, without chewing on it. After collection, saliva samples will be immediately stored in a freezer (−20°C) and will be registered at the UZ Ghent Biobank. sAA concentrations (nmol/l) will be determined from the collected saliva samples using enzyme-linked immunosorbent assay (ELISA) (Dresden LabService GmbH).

Continuous physiological monitoring will be performed during the entire lab assessment using the wireless and portable telemetry data acquisition system NeXus-10 MkI (Mind Media BV) with BioTrace+ software (Mind Media BV) and an MRI-compatible BIOPAC data acquisition system (BIOPAC Systems Inc) with AcqKnowledge software (BIOPAC Systems Inc). Respiratory rate (RR) will be measured using a piezoelectric stretch sensor placed around the chest and is expressed in the number of breaths per minute. Electrocardiography (ECG) will be used to measure heart rate (HR). HR will be expressed in beats per minute (bpm); HR variability (HRV) as the root mean square of successive differences between the beat-to-beat or NN intervals (RMSSD), and as the low (LF; 0.04–0.15 Hz) and high frequency (HF; 0.15–0.40 Hz) power components calculated from frequency analyses following fast Fourier transformation. The vertical lead II electrode placement will be used, which is in accordance with BioTrace+ for NeXus-10 software’s recommendations (Mind Media BV). In the MRI environment, the electrodes will be positioned closer together to minimize artifacts in the ECG trace [47]. Skin conductance (SC) will be measured using two electrodes placed on the non-dominant hand and expressed in micro siemens (µS). Skin temperature (ST) will only be measured in the lab (i.e., outside the MRI scanner) using one electrode placed on the non-dominant palmar side of the distal phalanx of the third digit and expressed in degree Celsius (°C). Systolic and diastolic blood pressure (BP) (Omron X3 Comfort) will be measured intermittently by using an inflatable cuff placed around the non-dominant upper arm, which will be supported and positioned at heart level. BP is expressed in millimeters of mercury (mmHg).

To establish a baseline for physiological monitoring, participants will focus on a fixation cross to minimize distractions. A similar fixation cross will be used during MRI scans, specifically between the pain stimuli. Before and after the acute stress induction in the lab, participants will be instructed to look at a neutral five-minute video to ensure consistency (e.g., in emotional arousal) in physiological monitoring across participants.

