### 2.6 Timing and conditions of stress level assessments.

Stress-related questionnaires will be acquired ten days before and throughout the experiment. Induced stress responses will be assessed in the lab (i.e., outside the MRI). VAS scores for stress will be administered before and after the acute stress induction. The PANAS will be administered at baseline, before and after the acute stress induction and the PASA will be administered before the acute stressor induction. Saliva samples will be collected at arrival (t1), prior to (t2), immediately after (t3), 15 minutes after (t4) and 50 minutes after (t5) the end of acute stress induction. RR, ECG, SC and ST assessments prior to and following the stress induction will be taken over five-minute windows [48,49]. BP will be measured at baseline, before stress induction, immediately after stress induction and five, ten and fifteen minutes after stress induction.

Acute stress will be induced using the Trier Social Stress Test (TSST), which is considered a gold standard to induce psychosocial stress without using a physical stressor (pain) [50]. The TSST consists of a brief instruction, a five-minute preparation phase, a five-minute social speaking task and a five-minute mental arithmetic task. The task includes negative feedback from a jury and a camera positioned in front of the participant. Participants will be instructed to look directly at the jury or the camera. They will be falsely informed that their behavior and facial expressions will be recorded and analyzed afterwards. Since habituation of the TSST might occur for the reassessment (at six-month follow-up), different social speaking and mental arithmetic tasks will be employed (e.g., job interview, ideal mentor; subtracting 17 from 2043 or from 1431) [51].

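### The blood pressure cuff sits upstream of the finger temperature and skin conductance sensors, and its five-minute cycle leaves no clear five-minute skin window in the first 15 minutes after the stressor

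*Protocol article*

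**What the plan says.** Section 2.4.2 of the protocol article fixes the limb for each device:

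- Skin conductance: "Skin conductance (SC) will be measured using two electrodes placed on the non-dominant hand".
- Skin temperature, in the lab only: "using one electrode placed on the non-dominant palmar side of the distal phalanx of the third digit".
- Blood pressure: "will be measured intermittently by using an inflatable cuff placed around the non-dominant upper arm".

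The same section says of the recording: "Continuous physiological monitoring will be performed during the entire lab assessment". It also describes the viewing condition before and after the stressor: "participants will be instructed to look at a neutral five-minute video to ensure consistency".

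Section 2.6 sets the timing. For the cuff: "BP will be measured at baseline, before stress induction, immediately after stress induction and five, ten and fifteen minutes after stress induction". For the other signals: "RR, ECG, SC and ST assessments prior to and following the stress induction will be taken over five-minute windows". It does not give the minute at which the post-stress window opens, nor its order relative to the cuff readings.

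**The concern.** An upper-arm cuff restricts arterial flow to the forearm and hand while it is inflated. Both skin sensors lie downstream of it. Finger temperature is informative about sympathetic activity because it follows peripheral blood flow, and that is what the cuff interrupts. Cooling under the cuff can resemble stress-related vasoconstriction, and rewarming after deflation can resemble recovery.

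Reactivity to acute stress and recovery from it are named in the primary aim, and the hypotheses in section 2.11 turn on blunted reactivity and prolonged recovery. If inflations fall inside the window from which ST is averaged, that marker mixes the stress response with a measurement artefact. The same may apply to SC, though the route is less clear. Heart rate, respiratory rate and the salivary measures do not depend on which arm carries the cuff, so the issue is confined to two of several autonomic markers.

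**Working it through.** The plan states no figure to reproduce here. The check is one of timing.

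**Inputs**

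- Cuff readings after the stressor: 0, 5, 10 and 15 minutes (section 2.6).
- Readings up to the stressor: two, at baseline and before induction (section 2.6).
- Skin window: W = 5 minutes (section 2.6).
- Cuff cycle d: 0.5 to 1.5 minutes. This is an assumption; the document gives no value.

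**Step 1: free time between readings.** Readings start 5 minutes apart, so the gap is 5 − d. A clear window needs 5 − d ≥ 5, which fails for every d above zero.

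**Step 2: overlap.** All window starts from 0 to 15 minutes after the stressor were checked on a 0.01-minute grid. For starts in the first 10 minutes, the time within a cuff cycle averages d, so the share of the window is d/5.

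| d (min) | Free gap 5 − d (min) | Windows starting at 0–15 min that overlap a cycle | Share of window, d/5 |
|---|---|---|---|
| 0.5 | 4.5 | 100% | 10% |
| 0.75 | 4.25 | 100% | 15% |
| 1.0 | 4.0 | 100% | 20% |
| 1.5 | 3.5 | 100% | 30% |

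**Step 3: the most favourable case.** If a reading is treated as having zero length, only windows starting at exactly 0, 5, 10 or 15 minutes avoid overlap, and those directly abut a reading. If the nominal times are loosened so that a full window fits between two readings, it still opens straight after deflation, while the hand is reperfusing.

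**Step 4: first window clear of inflation.** This starts at 15 + d, that is 15.5 to 16.5 minutes after the stressor.

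**Step 5: exposure before and after.** Total cuff time is 2 × d = 1 to 3 minutes up to the stressor and 4 × d = 2 to 6 minutes after it. These totals cover the whole period. A single five-minute window holds about one reading, so they do not give the imbalance between one pre-stress and one post-stress window.

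**The case against.** The strongest reply is that overlap is inferred and not stated. Section 2.6 does not fix the window to the minute, and section 2.3 refers the detailed order to Fig 1 and Table S1, which are not available here. The window could follow the 15-minute reading, or the 0- and 5-minute readings could bracket it. The first option avoids inflation, but it moves the window beyond the first 15 minutes after the stressor. The second leaves the window abutting a deflation. So the objection limits the claim without removing it.

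A reader might infer from four readings after the stressor and fewer before it that the artefact cannot cancel in the pre-post change. The document does not support that. Two readings precede the stressor, and one pre-stress and one post-stress window may each contain about one reading. Unequal exposure would matter only if several windows covered the recovery period, which section 2.6 does not say.

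A reader might also infer a bias between groups, for example if inflation is more painful or arousing in widespread pain. All groups share the schedule, and nothing in the document shows a differential response. Any arousal response in SC would also persist with the cuff on the other arm.

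It can further be said that artefact rejection belongs in an analysis plan, and that a condensed article need not describe it. That is fair, and its absence is not the point. The point is a stated placement combined with a stated schedule. Because recording is continuous, an analysis plan can remove affected segments, but it cannot restore a full undisturbed five-minute window in the first 15 minutes.

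Finally, changing the cuff arm is not free. Section 2.7.2 applies the temporal summation (TSP) stimulus and the conditioned pain modulation (CPM) test stimulus to the dominant forearm, and section 2.7 has pain testing before and after stress. This objection stands and shapes the fix.

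**Conclusion.** The point holds as a measurement weakness of limited scope. With the cuff on the sensor arm and readings every five minutes, a five-minute skin window in the first 15 minutes after the stressor overlaps or directly abuts at least one inflation. For an assumed cycle of 0.5 to 1.5 minutes, about 10% to 30% of the window lies within a cuff cycle, before reperfusion is counted. Flow need not be fully stopped throughout that time, so this is a share of samples exposed and not a measure of error.

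The consequence is clearest for finger temperature and less certain for skin conductance. The document gives no basis for a bias in degrees Celsius or microsiemens, for its pre-post imbalance, or for a difference between groups. It would be too strong to say that the post-stress readings are certainly contaminated or that the stress response is shifted in every participant. The correction is worth making because it is cheap, not because a large bias has been shown.

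**What to change.** **For all participants, including those already tested.** Before averaging, exclude ST samples (and SC samples) recorded during each inflation and for a fixed interval after deflation. Apply the identical rule to the pre-stress and post-stress windows. Set the interval before groups are compared. This needs the inflation times to be identifiable in the continuous recording.

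The cost is fewer samples. With one cycle removed, 3.5 to 4.5 of the 5 minutes remain, less the chosen post-deflation interval. This step is sufficient on its own if the sponsor prefers not to change procedure mid-study.

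**Optional, for participants not yet tested at baseline.** Place the cuff on the arm opposite the sensors, which takes all four post-stress inflations off the sensor arm. Two conditions apply:

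- Keep inflations clear of the TSP and CPM tests on the dominant forearm.
- Keep each longitudinal participant's cuff arm the same at six months as at baseline.

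Recruitment began on 8 February 2025, so a switch leaves cuff side partly confounded with enrolment date. A covariate for cuff side would not fully separate the two. The switch also would not remove any arousal response to the squeeze itself.

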### 2.5 Hormonal stress markers

#### 2.5.1 HPA axis – acute stress hormone levels.

Cortisol and oxytocin concentrations (pg/µl) will be determined from the collected saliva samples using the same procedures as mentioned for salivary alpha-amylase in 4.2. These hormones and alpha-amylase will be analyzed with liquid chromatography with coupled tandem mass spectrometry (LC-MS/MS) method (Dresden LabService GmbH).

#### 2.5.2 HPA axis – chronic stress hormone levels.

Long-term stress, over the last three months, will be assessed by means of hair cortisol concentrations (pg/mg). One sample will be taken at the start of the experiment by cutting hair from the posterior vertex region (i.e., ± 0.5 cm^2^, three centimeters (cm) in length covers three months). Samples will be collected in aluminum foil, stored in a dry and dark place, and analyzed by the LC-MS/MS method (Dresden LabService GmbH).

### 2.6 Timing and conditions of stress level assessments.

Stress-related questionnaires will be acquired ten days before and throughout the experiment. Induced stress responses will be assessed in the lab (i.e., outside the MRI). VAS scores for stress will be administered before and after the acute stress induction. The PANAS will be administered at baseline, before and after the acute stress induction and the PASA will be administered before the acute stressor induction. Saliva samples will be collected at arrival (t1), prior to (t2), immediately after (t3), 15 minutes after (t4) and 50 minutes after (t5) the end of acute stress induction. RR, ECG, SC and ST assessments prior to and following the stress induction will be taken over five-minute windows [48,49]. BP will be measured at baseline, before stress induction, immediately after stress induction and five, ten and fifteen minutes after stress induction.

Acute stress will be induced using the Trier Social Stress Test (TSST), which is considered a gold standard to induce psychosocial stress without using a physical stressor (pain) [50]. The TSST consists of a brief instruction, a five-minute preparation phase, a five-minute social speaking task and a five-minute mental arithmetic task. The task includes negative feedback from a jury and a camera positioned in front of the participant. Participants will be instructed to look directly at the jury or the camera. They will be falsely informed that their behavior and facial expressions will be recorded and analyzed afterwards. Since habituation of the TSST might occur for the reassessment (at six-month follow-up), different social speaking and mental arithmetic tasks will be employed (e.g., job interview, ideal mentor; subtracting 17 from 2043 or from 1431) [51].

Non-induced stress system functioning will be assessed at home. Participants will collect saliva samples for three (consecutive) days. Samples at home will be acquired directly after awakening (timepoint at home one or h1), 30 minutes after awakening (h2), 45 minutes after awakening (h3), at 16.00h (h4) and at 21.00h (h5). This will allow characterization of the first sample (h1), the cortisol awakening response (CAR) (mean increase = (h2 + h3/ 2*h1)), and basal cortisol levels throughout the day (Area Under the Curve (AUC) h1-h5) [52]. Self-collection has been previously used in chronic MSK pain [53]. Adherence to the instructions will be assessed, and the timing of sampling will be verified through documentation of the timepoint (by taking a picture of the sample with a timestamp) at which each sample is collected.

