**Aims:**

The primary aim of this study is to characterize stress system (dys)functioning (i.e., including basal levels, reactivity and recovery to acute stress, and chronic stress levels) in musculoskeletal pain groups with varying pain duration and extent, and to investigate the interaction between stress and pain at the psychosocial, (psycho)physiological and neural level. The secondary aim is to define the contribution of stress to pain trajectories, including chronification and recovery.

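### The formula printed for the cortisol awakening response is not the mean increase it is labelled as, under any bracketing

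*Protocol article*

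**What the plan says.** The derivation is in section 2.6 of the protocol article, on timing and conditions of stress assessment. Its purpose is stated as "Non-induced stress system functioning will be assessed at home". The three samples that enter the formula are:

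- h1, taken "directly after awakening (timepoint at home one or h1");
- h2 and h3, taken "30 minutes after awakening (h2), 45 minutes after awakening (h3").

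Three summaries are then listed: the first sample itself, "the cortisol awakening response (CAR) (mean increase = (h2 + h3/ 2*h1")), and "basal cortisol levels throughout the day (Area Under the Curve (AUC) h1-h5"). Section 2.5.1 gives the unit: "Cortisol and oxytocin concentrations (pg/µl) will be determined from the collected saliva samples".

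No other section gives a second or corrected formula for the awakening response. Where the article defines other change scores, it writes a plain difference, for example "Δ self-perceived stress = post-stressor VAS-scores – pre-stressor VAS-scores" in section 2.4.1. Affect (2.4.1), self-perceived pain (2.7.1) and conditioned pain modulation (2.7.2) are handled in the same way.

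**The concern.** The label and the sample definitions together fix what a mean increase is: the average of the two post-awakening samples minus the awakening sample. The printed expression does something else. The article chose to publish the derivation, so this is a wrong statement and not detail left to an analysis plan.

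At stake is one outcome. The primary aim covers stress system functioning "including basal levels, reactivity and recovery to acute stress, and chronic stress levels", and the awakening response is one of three summaries drawn from the home samples. An analyst who codes the line as printed gets a number that is not an awakening response. Two analysts who repair it differently get outcomes on different scales, with different no-change values.

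**Working it through.** **Inputs.** The formula and the definitions of h1, h2 and h3 come from section 2.6, and the concentration unit from section 2.5.1. The profiles below are illustrative values in arbitrary units, not figures from the article.

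**Target implied by the label:** MI = (h2 + h3)/2 − h1.

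**Possible readings of the printed expression:**

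- (a) h2 + (h3/2) × h1, the ordinary operator order
- (b) h2 + h3/(2 × h1)
- (c) (h2 + h3)/(2 × h1)
- (d) ((h2 + h3)/2) × h1

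Readings (c) and (d) already need a bracket that is not printed.

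**Test 1: a flat profile must give 0.** With h1 = h2 = h3 = 10:

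- MI = 20/2 − 10 = 0
- (a) 10 + 5 × 10 = 60
- (b) 10 + 10/20 = 10.5
- (c) 20/20 = 1.0
- (d) 10 × 10 = 100

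**Test 2: a fall must be negative, and equal absolute rises must give equal values.**

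| h1/h2/h3 | MI | (a) | (b) | (c) | (d) |
|---|---|---|---|---|---|
| 10/7/6 | −3.5 | 37 | 7.3 | 0.65 | 65 |
| 5/10/11 | 5.5 | 37.5 | 11.1 | 2.10 | 52.5 |
| 10/15/16 | 5.5 | 95 | 15.8 | 1.55 | 155 |
| 20/25/26 | 5.5 | 285 | 25.65 | 1.275 | 510 |

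No reading is negative for the falling profile, and none is constant over the three profiles with the same rise.

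**Test 3: units.** Reading (a) adds a concentration to a squared concentration, (b) adds a concentration to a unit-free number, and (d) is a squared concentration. Only (c) is dimensionally coherent, and it is unit-free. The effect on (a) is visible if the flat profile is expressed in units ten times larger (1/1/1). The value becomes 1 + 0.5 × 1 = 1.5, where a quantity in concentration units would have gone from 60 to 6.

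**Is it only a wrong operator?** No. Replacing the multiplication sign by a minus and leaving the rest gives h2 + h3/2 − h1, which is 10 + 5 − 10 = 5 for the flat profile. Both the missing bracket and the operator must be changed to reach MI.

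**How the ratio relates to the label.** Algebraically, (h2 + h3)/(2 × h1) = 1 + MI/h1. So (c) is a fold value. It carries the same information as a relative increase, but it is centred on 1 and is not an increase as it stands.

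**The case against.** The strongest reply is that the intended quantity may be relative. Moving a single bracket gives (h2 + h3)/(2 × h1) and keeps every printed symbol, whereas the difference needs a moved bracket and a changed operator. The term mean increase does not say absolute or relative, and the sentence cites a source that is not at hand. This stands as a reason to leave the authors the choice. It does not rescue the printed line, because a ratio still needs the bracket and a different label.

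Several stronger readings are tempting, but the article does not support them.

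- *A reader might infer that the outcome will be computed wrongly.* The line looks like a misprint, and the article cannot show what the analysts will code. The error follows only if the formula is used as printed.
- *A reader might infer that a main or primary outcome is damaged.* No outcome is designated as primary, and section 2.11 states no hypothesis about the awakening response. The sample size in section 2.10 rests on a general effect size and not on this measure.
- *A reader might infer that the planned group differences in basal cortisol will leak into the awakening response.* Section 2.11 speaks of basal cortisol and never names h1, and section 2.6 attaches the basal level through the day to the area under the curve.
- *A reader might infer that a ratio is always distorted by the awakening level and a difference never is.* That holds only if rises are additive. If profiles scale in proportion, such as 5/7.5/7 and 20/30/28, the ratio is 14.5/10 = 58/40 = 1.45 in both. The difference is then 7.25 − 5 = 2.25 against 29 − 20 = 9.

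**Conclusion.** The printed formula is wrong as written. No bracketing of it gives an increase from h1: a flat profile returns 60, 10.5, 1.0 or 100 where 0 is required. This needs no assumption beyond the label and the article's own sample definitions. The sizes of the discrepancies are illustrative, because they depend on the chosen profiles.

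The consequence is confined to one of three listed home-cortisol summaries, and it is conditional on the formula being followed. The other two summaries, the sampling schedule and the sample size do not depend on it. The article's habit of writing change scores as differences makes (h2 + h3)/2 − h1 the natural reading of the label, but it does not exclude a relative measure.

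**What to change.** In section 2.6, replace the expression with (h2 + h3)/2 − h1. This matches the label and the form of the article's other change scores. If a relative measure is intended, print (h2 + h3)/(2 × h1) with both brackets and call it a ratio to the awakening sample, not an increase. Carry the same definition into any analysis plan, and check the scoring script against it before analysis.

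The cost is one line of text and one check of code. The stored sample values are enough to compute either version, so design, recruitment and data collection do not change.
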